### Thromboelastography (TEG)

During the surgical procedure the transfusion will be guided by TEG of ROTEM (Rotational Elastometry). TEG/ROTEM has to be performed at least twice during the surgical procedure:

– 15 minutes after start anhepatic phase

– 30 minutes after start reperfusion phase

### Parameters during surgery

The following data will be recorded for participating patients:

– Donor characteristics

– Recipient characteristics

– Liver transplantation technique (conventional versus piggy-back)

– Use of veno-venous bypass

– Data on timing (cold-ischemia time, warm-ischemia time, duration anhepatic phase etc.)

– Surgical abnormalities and technical difficulties including heavy blood loss due to diffuse oozing or accidental vascular injury

– Ascites upon opening abdomen

– Lowest PH, Ca2+, lactate, temperature (during and within the first 24 hours of surgery)

– Transfusion requirements (during and within the first 24 hours of surgery)

– Medication (during and within the first 24 hours of surgery)

– Colloid/Crystalloid/Albumin/Gelatine infusion (during and within the first 24 hours of surgery)

### Laboratory parameters

– Prior to the OLT, an INR measurement will be performed to check if the patient still meets the inclusion criteria. After administration of the IMP, no routine INR measurements will be performed by the anaesthesiologist during the course of surgery, since measuring the INR will likely unblind the anaesthesiologist for the intervention.

– A blinded INR measurement will be performed (see section ‘Additional Study Procedures’) by an independent assistant 30 minutes after administration of the intervention and will only be available for an independent researcher. These measurements will be used during the interim analysis.

– Troponin levels are recorded just before and after surgery at ICU admission and the day after surgery, and in case of a suspected event due to clinical symptoms or ECG abnormalities during routine testing according to routine clinical practice.

– During OLT other laboratory and coagulation measurements (with the exception of the PT) may be performed according to local practice.

– Post-operatively, laboratory measurements presented in Table 4 will be performed from day 1–7 in the first week which is currently common practice in participating centers. From the second week, these laboratory measurements are only obligatory on day 14 and 30 (within a 24 hour timeframe).

**Table 4 T4:** Laboratory parameters

**Hemostasis**	**Hematology**	**Clinical chemistry**	
Prothrombin Time	Hemoglobin (Hb)	C-reactive protein	Lactate dehydrogenase
Activated Partial Thromboplastin Time	Hematocrit	Glucose	Aspartate-aminotransferase
		Creatinine	Alanine-aminotransferase
Fibrinogen	Platelets	Urea	Alkaline Phosphatase
International Normalized Ratio	Leucocytes	Sodium	Albumin
		Potassium	Calcium
		gamma-glutamyltransferase	

### Surgical and anesthesiological procedure

There is no change in surgical or anesthesiological procedure from the current practise in participating centers.

### Postoperative procedure

The patient will be followed postoperatively according to local practise:

– Low molecular weight heparin as prophylaxis for deep venous thrombosis.

– Daily laboratory measurements in the first week

– Ultrasound of the hepatic vessels within 24 hours of surgery, at day 3 and day 7 postoperative

### Additional study procedures

The following additional procedures are included for the study subjects and are not part of the local practice:

• Prior to intervention and after intervention viral safety blood samples will be collected

• During the OLT-procedure, 30-minutes after administration of the IMP, a blinded INR measurement will be performed. The result of this measurement will be kept blinded for the anesthesiology and surgical team but will be recorded by an independent researcher. These results will be used during the interim analysis to investigate whether the INR in the PCC-group reached a value below 1.5 or whether the dosages of PCC need adjusting.

• Troponin levels are recorded just before and after surgery at ICU admission and the day after surgery.

• At 12 time points an additional blood sample will be collected from the patient for satellite studies on e.g. thrombin generation and fibrinolysis after completion of this trial. See Table 5 for the time points.

**Table 5 T5:** Time point of additional blood sample collection

**Phase under study**	**Timing of blood sample collection**
Baseline	1. upon admission for OLT
Intervention	2. prior to intervention, after induction of anaesthesia
	3. 30 minutes after intervention
Pre-anhepatic phase	4. 1 hour post-intervention
	5. 2 hours post-intervention
Anhepatic phase	6. 15 minutes after start anhepatic phase
Reperfusion phase	7. 15 minutes after start reperfusion phase
	8. end of surgery
Follow-up	9-12. postoperative days 1, 3, 5, and 11

• On day 3 and 7 physical examination is performed with special attention to clinical venous thromboembolic events. In case of suspected deep venous thrombosis Doppler ultrasonography and on suspicion of pulmonary embolism a CT-angiography will be performed. If indeed a thrombotic complication occurs in the deep venous system or in the pulmonary arterial circulation, therapy will be initiated according to the local practice and with regards to the patient’s post-transplant status.

• A 12-lead electrocardiogram performed on the day of treatment prior to the intervention and product administration and 3 and 7 days post surgery and on clinical indication.

### Statistics

#### Sample size

Based on experience in the participating centers, it is assumed that cirrhotic patients undergoing OLT have a mean transfusion requirement of 8 U RBC (SD = 4 U). This data was derived from a retrospective data analysis of transfusion requirements during OLT in the UMCG over 2008–2011. The sample size of this trial was chosen to detect a reduction of 2 units of RBCs with approximate 80% power. The following statistical formula for sample size calculation was used to determine the sample size. N = 16***σ***^2^ / d^2^.

With an expected 10% withdrawal or loss of study subjects we concluded that 70 patients in each group are required to demonstrate a difference between placebo and PCC administration.

#### Interim analysis

One interim analysis will be performed by the trial statistician after 70 patients (50% of the sample size) have been included.

The Sponsor has chosen different boundaries for the different endpoints for the interim analysis, giving more significance to early unfavourable trends then to early beneficial trends. These boundaries are more used as guidelines rather than absolute rules.

For the efficacy endpoint, the O’Brien-Fleming sequential boundary will be used to correct for the instability of efficacy parameters at the beginning of the trial. For a total number of 2 planned statistical analyses and one planned interim analysis a Z-value of 3 with a P of 0.0027 will be used to determine statistical significance during the interim analysis. During the final analysis a Z-value of 2 and a P-value of 0.045 will be used to determine statistical significance.

For the safety endpoints, we have chosen to use the Pocock sequential boundary, dictating a Z-value of 2 and thus a P-value of 0.045 to determine statistical significance in harm between the two groups during the interim analysis as well as the final analysis.

Besides the efficacy and safety endpoint, during the interim analysis, sample size assumptions will be monitored based on the transfusion requirements in the placebo- group and if needed the sample size will be adjusted. Also, results from the blinded INR-measurements 30 minutes after intervention in de PCC-group will be used to determine whether the PCC-dose sufficiently lowers the INR in this patients group of whether the dose needs adjusting during the further conduct of this trial.

The trial may be stopped early due to one of the following situations:

– Unacceptable safety concerns: The analysis shows significant (serious) adverse events in the treatment group compared to the placebo group.

– The results on the endpoint between treatment-group and placebo group are inconclusive and it is expected that no significance will be reached.

– The interim analysis shows a clear benefit in the treatment group compared to the placebo group.

– In case new external information arises that convincingly answers the study question or raises serious safety issues.

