#### Statistical analysis

Statistical analyses will be performed using the statistical software package SPSS 19.0 (SPSS Inc, Chicago, IL). Two-sided tests using the 5% critical level will be used throughout. The Mann–Whitney U test will be used to determine a significant difference in transfusion needs between the 2 groups. Intergroup categorical data will be compared using Chi-square or Fisher exact test. Intergroup continuous data will be analyzed with parametric or non-parametric analysis methods depending on the presence/absence of Gaussian distribution. If required, appropriate corrections for multiple comparisons will be applied. Independent risk factors for bleeding diathesis and transfusion during OLT will be identified using uni- and multivariate logistic regression analysis. All variables that reached a P < = 0.05 in the univariate analysis will be included in the multivariate linear regression analysis. P <0.05 will be considered statistically significant.

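### The final primary test has two unreconciled significance thresholds (P 0.045 and P < 0.05); separately, the pair labelled O'Brien-Fleming uses P-values taken from Z-values rounded to integers

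*Protocol article*

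**What the plan says.** Two sections of the protocol article set the level for the final primary comparison.

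- **Interim analysis.** There is one interim look: "One interim analysis will be performed by the trial statistician after 70 patients (50% of the sample size) have been included". The rule is named: "For the efficacy endpoint, the O’Brien-Fleming sequential boundary will be used". For the interim, "a Z-value of 3 with a P of 0.0027 will be used to determine statistical significance during the interim analysis". For the end of the trial, "During the final analysis a Z-value of 2 and a P-value of 0.045 will be used to determine statistical significance". The section also says of its boundaries: "These boundaries are more used as guidelines rather than absolute rules".
- **Statistical analysis.** The general level is "Two-sided tests using the 5% critical level will be used throughout". The next sentence names the primary test: "The Mann–Whitney U test will be used to determine a significant difference in transfusion needs between the 2 groups". After the sentences on categorical data, continuous data and risk-factor regression, the paragraph ends: "P <0.05 will be considered statistically significant".

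The Statistical analysis section does not mention the interim look, the 0.045 level or any exception for the primary endpoint (RBC units during surgery and the first 24 hours from ICU arrival).

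**The concern.** The final level was lowered to 0.045 because the primary endpoint is also tested at the interim. If the 5% level is then applied to the same test, the adjustment disappears. A reader holding only this document cannot say with certainty whether a final P of 0.047 is a positive trial. If the question is settled only after the P-value is known, the choice of section decides the primary conclusion.

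A second, independent point concerns the name of the rule. Someone who implements O'Brien-Fleming for two equally spaced looks gets different thresholds from someone who implements the printed numbers. This mismatch does not cause the conflict between 0.045 and 0.05, which would exist even if the printed pair were exact.

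**Working it through.** **Inputs** (all from the Interim analysis and Statistical analysis sections): two analyses; interim at 70 of 140 patients, so information fraction t = 0.5; stated boundaries Z = 3 (P 0.0027) and Z = 2 (P 0.045); general two-sided level 5%.

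**Step 1. Reproduce the plan's Z-to-P conversions**, with P = 2 × (1 − Φ(Z)).
- Z = 3 gives P = 0.0027, as stated.
- Z = 2 gives P = 0.0455, printed as 0.045. A P of exactly 0.045 corresponds to Z = 2.005.

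So the P-values come from the whole-number Z-values.

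**Step 2. Compare with the named rule.** A two-look O'Brien-Fleming boundary has c1 = c2 / √t. At t = 0.5 the ratio c1/c2 must be √2 = 1.414; the stated ratio is 3/2 = 1.5. The overall two-sided error of a pair (c1, c2) is

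1 − ∫ from −c1 to c1 of φ(x) × [Φ((c2 − √t·x)/√(1 − t)) − Φ((−c2 − √t·x)/√(1 − t))] dx.

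Setting c1 = √2 × c2 and solving for an overall 0.05 gives c2 = 1.977 (P 0.0480) and c1 = 2.797 (P 0.0052). Rounded to integers these are 2 and 3, which explains the printed figures. The printed interim P (0.0027) is about half of 0.0052, and the printed final P (0.045) is below 0.0480.

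**Step 3. Overall two-sided error of the rules the text can support**, from the same integral.

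| Interim | Final | Overall error |
|---|---|---|
| Z = 3 | Z = 2 | 4.64% |
| P 0.0027 | P 0.045 | 4.59% |
| Z = 3 | P < 0.05 (Z = 1.96) | 5.08% |

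**Step 4. Final level that spends exactly 5% if the interim stays at Z = 3.** Solving the integral for c2 with c1 = 3 gives Z = 1.967, P = 0.0491.

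**Step 5. Where the readings give different answers.**

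| Result | Printed numbers, Interim analysis | Exact O'Brien-Fleming | Statistical analysis (P < 0.05) |
|---|---|---|---|
| Interim P = 0.004 | not crossed | crossed | no separate interim rule |
| Final P = 0.047 | not significant | significant | significant |
| Final P = 0.049 | not significant | not significant | significant |

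**The case against.** The strongest reply is that a specific rule governs over a general one. The interim section names the efficacy endpoint, the final analysis, a Z and a P. The other section is a general paragraph, and its closing criterion directly follows the regression sentences. The 5% can also be read as the overall level that the interim section divides between two looks. Taken literally, a 5% level for every test would cover the interim look too, which cannot be intended. This is probably what the authors meant. It does not settle the matter, because the 5% sentence immediately precedes the one specifying the primary test, allows no exception and does not point back. The interim section also describes its own boundaries as guidelines.

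On the label, the reply largely stands. Both the classical pair (2.797, 1.977) and the O'Brien-Fleming-type spending version at 50% information (2.963, 1.969; P 0.0031, 0.0490) round to 3 and 2, and the printed pair is conservative.

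Three stronger readings are tempting, but the document does not support them:
- **Error is uncontrolled because the boundaries are guidelines.** The document proposes no looser efficacy stop. It prints Z = 3 for the interim and lists a clear benefit as the ground for stopping. Not stopping after a crossing does not by itself inflate the error.
- **The mislabelled boundary raises the false-positive risk.** As printed, it lowers it, to 4.64%.
- **The trial is underpowered because the interim was ignored.** The Sample size section claims only about 80%. With 70 × 0.9 = 63 evaluable per arm, SD 4 and a difference of 2 units, the normal approximation gives 80.1% at 0.05 and 79.0% at 0.0455, a loss within that wording.

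**Conclusion.** The point holds as a conflict of wording that should be fixed, not as a material threat to error control. Final primary P-values from 0.045 to below 0.05 are classified differently by the two sections. The least favourable reading of the text exceeds 5% by 0.08 percentage points (5.08%), and the printed pair falls short of 5% by 0.36 points (4.64%). What matters is that the criterion for success on the primary endpoint is not unique in advance. The name of the boundary and its printed values also disagree, a secondary matter.

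The figures assume an interim at exactly half the information, one interim look, a primary statistic that is approximately normal with the usual correlation √0.5 between looks, and an unchanged total of 140. The protocol allows the sample size to be adjusted at the interim. If it is, the information fraction changes and the levels need recomputing.

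**What to change.** State one decision rule for RBC units in the Interim analysis section, choosing one of these:

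- **O'Brien-Fleming, exact:** interim Z = 2.797 (two-sided P 0.0052), final Z = 1.977 (P 0.048).
- **Interim kept at Z = 3 (P 0.0027):** name it a Haybittle-Peto-type rule and test the final analysis at P 0.049 (Z = 1.967).

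Then, in the Statistical analysis section, limit the two-sided 5% level and the P < 0.05 criterion to the other endpoints, and add a cross-reference saying that the primary Mann-Whitney test uses the final level from the Interim analysis section.

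The cost is a few words in the protocol and the same words in any analysis plan, with no change to the sample size or the data collected. Either option is slightly less strict at the final analysis than the printed 0.045, so nothing is lost there. The change should be made before anyone sees comparative data.

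### The Z = 2 / P = 0.045 safety boundary at both looks is not the two-look Pocock value at 5% (Z = 2.178 / P = 0.0294); false-harm probability is about 3.8% per endpoint, not 2.5%

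*Protocol article*

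**What the plan says.** The protocol article, under Interim analysis, plans one interim look "after 70 patients (50% of the sample size) have been included" and then the final analysis. On safety it names a "Pocock sequential boundary, dictating a Z-value of 2 and thus a P-value of 0.045" as the threshold for declaring harm, and it applies this value "during the interim analysis as well as the final analysis".

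Efficacy has a separate O'Brien-Fleming rule: Z = 3 (P = 0.0027) at the interim, then: "During the final analysis a Z-value of 2 and a P-value of 0.045 will be used to determine statistical significance".

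The same section says that the boundaries serve as guidance rather than binding rules, and that early unfavourable trends are meant to count for more than early favourable ones. Under Statistical analysis, the general error level is given as: "Two-sided tests using the 5% critical level will be used throughout". The article gives no other overall error rate for safety.

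**The concern.** A Pocock boundary uses one critical value at every look, chosen so that the error over all looks together equals a stated level. With more than one look, the nominal P at each look must be clearly below that level. A nominal P of 0.045 at each of two looks is too close to 5% for the two looks together to hold 5%.

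The article also uses the same pair, Z = 2 and P = 0.045, for the final efficacy look. That pair works there because the first efficacy look is very strict. It does not carry over to a rule that uses Z = 2 at both looks.

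Two things are at stake. A data monitoring board or reader who sees the name Pocock will assume 5% control across the looks. And a safety result with P between 0.0294 and 0.045 is significant by the printed number but not by the named method, so the text gives two answers to the same result.

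**Working it through.** **Inputs**
- Two looks, interim at 50% (Interim analysis). The Sample size section gives 70 per group, so 140 in total, and 70/140 = 0.5.
- Critical value for safety: Z = 2 at both looks (Interim analysis).
- Two-sided 5% (Statistical analysis).

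**Step 1: the plan's own pair.** The two-sided P for Z = 2 is 2 × (1 − Φ(2)) = 0.0455. Conversely, P = 0.045 corresponds to Z = 2.005. Z and P therefore agree with each other up to rounding. What does not reproduce is the claim that Pocock gives this value.

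**Step 2: the Pocock constant.** With no treatment effect, the statistics at the two looks are bivariate normal with correlation √0.5 = 0.707. Solve

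1 − P(|Z1| < c and |Z2| < c) = 0.05.

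The result is c = 2.178, nominal two-sided P = 0.0294. One-sided 2.5% gives the same constant. One-sided 5% gives 1.875. None of these conventions gives 2.

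**Step 3: the error of the printed rule (normal approximation, per endpoint).**

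| Rule at both looks | False harm (one direction) | Either direction |
|---|---|---|
| Z = 2 | 3.80% | 7.60% |
| P = 0.045 exactly (Z = 2.005) | 3.76% | 7.52% |
| Z = 2.178 | 2.5% | 5.0% |

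In the harm direction the ratio is 3.8/2.5 = 1.52.

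**Step 4: timing of the interim.** If the interim carries 30% to 70% of the final information instead of 50%, the two-sided error with Z = 2 twice runs from 8.2% down to 6.9%. It stays above 5% throughout.

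**Step 5: the efficacy rule for comparison.** Z = 3 then Z = 2 gives 4.64% overall, within 5%.

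**Step 6: dependence on the test.** The article allows chi-square or Fisher's exact test for categorical data. Both looks were simulated with 35 and then 70 patients per arm, 1,000,000 runs, and the same event rate in both arms. The event rates are assumptions; the article gives none. Overall two-sided error:

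| Event rate | Fisher, P ≤ 0.045 twice | Uncorrected chi-square, Z = 2 twice |
|---|---|---|
| 3% | 0.5% | 4.9% |
| 5% | 1.5% | 6.5% |
| 10% | 2.8% | 7.4–7.5% |
| 20% | 4.2% | 7.8% |
| 30% | 4.8% | 7.8% |

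The normal-approximation figure is thus about right for chi-square at event rates of 10% or more. It is too high for Fisher's test at every rate tried.

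**The case against.** The strongest reply is that a lenient harm boundary is intended. The section wants early unfavourable trends to weigh more, treats the boundaries as guidance, and an independent data monitoring board advises on the data. Flagging harm too readily is the protective direction. A constant critical value is also the Pocock shape, so Z = 2 twice can be read as a Pocock-type rule at a higher overall level, and the section states no overall level for safety.

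Much of this stands, and it limits how serious the point is. It does not rescue the sentence. The text does not say that a higher error is accepted; it says Pocock dictates Z = 2. The only level stated is 5%. The value is also used to decide significance at the final analysis, where no stopping judgement is involved. And a true Pocock boundary already weights early harm more than early benefit: 2.178 against 3 at the interim.

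Three stronger readings are tempting, and the documents do not support them.
- *The harm test has a 7.6% error.* That figure counts crossings where placebo looks worse. The threshold is stated for harm, so 3.8% against 2.5% is the relevant comparison.
- *The error always exceeds 5%.* Step 6 shows that it need not with Fisher's test.
- *The error reaches about 21% across safety endpoints.* This needs three independent endpoints, 1 − (1 − 0.076)³ = 0.21, a number the article does not give. A correct boundary would give 1 − 0.95³ = 0.14 on the same assumption, so most of it is ordinary multiplicity. The article also foresees corrections for multiple comparisons where required.

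**Conclusion.** The point holds as a wrong constant attached to a named method. At two-sided 5% with two equally spaced looks, Pocock gives Z = 2.178 / P = 0.0294, not Z = 2 / P = 0.045. The printed rule raises the false-harm probability per endpoint from 2.5% to about 3.8% (5% to 7.6% two-sided).

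This rests on the normal approximation, an interim at half the information, and reading the general 5% statement as the overall target for safety. That reading is fair, but the article does not make it explicit for sequential safety testing.

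A reader might infer that the trial's main result is compromised. It is not: the efficacy boundary is separate and holds 4.64%, and the safety slip errs on the cautious side. The sentence should be corrected, ideally before unblinded data are reviewed, but this is not a condition for the trial to be sound.

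**What to change.** Change one sentence under Interim analysis, in one of two ways:

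1. Keep Z = 2 / P = 0.045 at both looks as a deliberately sensitive harm guideline, remove the statement that Pocock dictates it, and give its overall error: about 3.8% for harm, 7.6% two-sided, per endpoint, by normal approximation. No decision threshold changes. The cost is a stated error rate that looks less favourable.
2. If 5% Pocock control is intended, print Z = 2.178 / P = 0.0294 at both looks. The cost is slightly lower sensitivity to harm.

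The first option fits the section's stated wish to weight unfavourable trends. Either one removes the conflict for results with P between 0.0294 and 0.045. Any analysis plan that repeats the sentence should be changed to match.

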**Discussion:**

Patients with advanced cirrhosis have reduced plasma levels of both pro- and anticoagulant coagulation proteins. Prothrombin complex concentrate is a low-volume plasma product that contains both procoagulant and anticoagulant proteins and transfusion will not affect the volume status prior to the surgical procedure. We hypothesize that administration of prothrombin complex concentrate will result in a reduction of perioperative blood loss and transfusion requirements. Theoretically, the administration of prothrombin complex concentrate may be associated with a higher risk of thromboembolic complications. Therefore, thromboembolic complications are an important secondary endpoint and the occurrence of this type of complication will be closely monitored during the study.

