## Methods/design

### Design and objectives

The study is designed as a multicenter, double blind, randomized placebo-controlled trial. The study is investigator-initiated.

The primary objective is to study the hemostatic efficacy of preoperative PCC administration in patients with cirrhosis and severe coagulopathy undergoing liver transplantation. The hemostatic efficacy will be primarily monitored by recording the need for RBC transfusion.

The secondary objective is to study the hemostatic safety of preoperative PCC administration in patients with cirrhosis undergoing liver transplantation. The hemostatic safety will be monitored by adverse event surveillance and laboratory measurements, with a special focus on thrombogenicity.

All study procedures during this study are summarized in Table 1.

**Table 1 T1:** Timing of study procedures

**Parameters**				**Timepoints**													
	**SEH**	**Surgical procedure**					**Postoperative days**										
		**Anesthesia**	**30 minutes after intervention**	**Pre-anhepatic phase**	**Anhepatic phase**	**Reperfusion phase**	**0/1**	**2**	**3**	**4**	**5**	**6**	**7**	**11**	**14**	**30**	
12-leads ECG	x	According to local protocol							x				x			
Lab	x						x	x	x	x	x	x	x		x	x
Troponin	x						x									
Plasma sample	x	x	**x**	**1 hour after intervention**	**15 minutes after start phase**	**15 minutes after start phase**	x		x		x			x		
				**2 hours after intervention**		**end of surgery**										
Viral safety	x															
TEG/ROTEM					**15 minutes after start phase**	**30 minutes after start phase**										
Blinded INR			**x**				x		x				x			
Ultrasound hepatic vessels		According to local protocol									first 24 h after surgery					
Registration transfusion products			**x**	**x**	**x**	**x**			x				x			
Physical examination with focus on thrombotic and ischemic events																

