### Endpoints

The primary endpoint will be the number of RBC units transfused during the OLT procedure and in the 24 hour post-surgery period, starting from arrival at the ICU. Other efficacy endpoints are (measured during surgery and during the 24-hour period post-surgery):

• The number of transfused units of fresh-frozen plasma

• The number of transfused units of platelet concentrate

• Fibrinogen concentrate administration

• Estimated blood loss

• Antifibrinolytic drugs

• Crystalloids or colloids administered

• Other escape medication used

• Estimated ascites loss

Safety is a secondary endpoint, safety parameters recorded are:

• All (Serious) Adverse Events with special focus on thromboembolic events

• General and liver-specific laboratory parameters

• Lowest pH, Ca++, lactate, temperature (during and within the first 24 h after surgery)

• Troponin levels, ECG and hepatic vessel ultrasound results

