• Escape medication: In case of a critical bleeding (by clinical judgment) during the liver transplantation procedure, treatment can be initiated in accordance with hospital guidelines and procedures e.g. antifibrinolytic drugs at habitual doses. All data on critical bleeding episodes should be reported as a serious adverse event. Type and amount of the escape medication and the justification will be recorded in the CRF.

• Enoxaparin or other low molecular weight heparin (LMWH): LMWH will be administered postoperatively as usual for deep venous thrombosis prophylaxis. Dosing will be according to routine local practice.

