#### Premature termination of the trial

The trial will be terminated prematurely if we find a high rate of Serious Adverse Events in the PCC-group during the interim analysis, possibly liable to the study product.

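### The written criteria for stopping for harm rest on undifferentiated serious adverse events, so a thromboembolic excess can be diluted and partly offset

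*Protocol article*

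**What the plan says.** The protocol article states the criterion for stopping for harm in two places.

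- Statistics, Interim analysis, first reason to stop: "The analysis shows significant (serious) adverse events in the treatment group compared to the placebo group".
- The section on premature termination speaks of stopping "if we find a high rate of Serious Adverse Events in the PCC-group during the interim analysis". It then narrows this, in the same sentence, to events "possibly liable to the study product".

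The Interim analysis section also sets a boundary of Z = 2 (P = 0.045) for the safety endpoints, at the interim and again at the final analysis. It calls the boundaries guidelines rather than fixed rules. The interim look comes after 70 patients.

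Other sections bear on what an SAE comparison contains.

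- Transfusion guidelines, escape medication: "All data on critical bleeding episodes should be reported as a serious adverse event".
- Abstract, Discussion: "We hypothesize that administration of prothrombin complex concentrate will result in a reduction of perioperative blood loss and transfusion requirements". The same paragraph names a higher thromboembolic risk as the possible cost.
- Design and objectives: safety is monitored "with a special focus on thrombogenicity".
- Endpoints: the first safety parameter is "All (Serious) Adverse Events with special focus on thromboembolic events".
- The main Discussion also calls thromboembolic complications a secondary and safety endpoint.

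**The concern.** The safety objective is about one kind of event, but the stopping criteria are worded for all serious events together. This has two effects.

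1. **Dilution.** Liver transplantation carries many serious events unrelated to the product. A difference in one component is harder to see in the total.
2. **Offset.** Critical bleeding is an SAE and is expected to fall on PCC if the product works. A fall in bleeding SAEs subtracts from a rise in thromboembolic SAEs.

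The interim analysis is meant to give more weight to early unfavourable trends than to favourable ones. A harm comparison on undifferentiated SAEs works against that aim, most of all when the product reduces bleeding. At stake is whether the one planned interim comparison can respond to the risk that the protocol singles out.

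**Working it through.** **The plan's own figures.** The stated formula gives 16 × 4² / 2² = 64 per group. Allowing for 10% loss gives 64 × 1.1 = 70.4 or 64 / 0.9 = 71.1, in line with the stated 70 per group. Half of 140 is 70 patients, so about 35 per arm at the interim. Z = 2 corresponds to a two-sided P of 0.0455, in line with the stated 0.045.

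**Inputs that are assumptions.** The protocol gives no SAE rates. I assume:

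- thromboembolism in 5% on placebo and 20% on PCC;
- critical bleeding halved on PCC, from 30%, 20%, 10% or 5%;
- other SAEs in 0% or 30% of patients, equal in both arms;
- independent components, each patient counted once.

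**Formula.** Any-SAE rate = 1 − (1 − thromboembolism)(1 − bleeding)(1 − other).

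Example with bleeding 30% to 15% and no other SAEs:

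- placebo: 1 − 0.95 × 0.70 = 33.5%
- PCC: 1 − 0.80 × 0.85 = 32.0%

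With 30% other SAEs:

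- placebo: 1 − 0.95 × 0.70 × 0.70 = 53.5%
- PCC: 1 − 0.80 × 0.85 × 0.70 = 52.4%

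**Chance of a harm signal.** This is the exact binomial probability that the pooled two-proportion Z is at least 2 in the direction of harm.

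| Comparison | Bleeding, placebo to PCC | Other SAEs | Rate, placebo vs PCC | 35 per arm | 70 per arm |
|---|---|---|---|---|---|
| Thromboembolism alone | – | – | 5% vs 20% | 47% | 79% |
| Any SAE | 30% to 15% | 0% | 33.5% vs 32.0% | 1.7% | 1.4% |
| Any SAE | 30% to 15% | 30% | 53.5% vs 52.4% | 1.7% | 1.9% |
| Any SAE | 20% to 10% | 0% | 24.0% vs 28.0% | 5.4% | 7.3% |
| Any SAE | 20% to 10% | 30% | 46.8% vs 49.6% | 3.6% | 5.3% |
| Any SAE | 10% to 5% | 0% | 14.5% vs 24.0% | 16% | 28% |
| Any SAE | 10% to 5% | 30% | 40.2% vs 46.8% | 7.0% | 12% |
| Any SAE | 5% to 2.5% | 0% | 9.8% vs 22.0% | 28% | 50% |
| Any SAE | 5% to 2.5% | 30% | 36.8% vs 45.4% | 9.7% | 17% |
| Any SAE | none | 30% | 33.5% vs 44.0% | 13% | 24% |

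With Fisher's exact test at P ≤ 0.045 the interim figures are lower throughout: 30% for thromboembolism alone, and 0.9% to 16% for any SAE across the rows in which bleeding is halved.

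**Separating the two effects at the interim.** A 30% background with no bleeding SAEs cuts detection from 47% to 13%; that is dilution alone. On top of that background, halving bleeding takes 13% down to 9.7% (from 5%) or 1.7% (from 30%). With no other SAEs and bleeding at 30% in both arms, detection is also 13%; halving bleeding on PCC then brings it to 1.7%. Dilution is thus a large part of the loss. The offset becomes decisive only when critical bleeding is common.

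**The case against.** The strongest reply is that nowhere does the protocol say all SAEs are summed into one count and only that count is tested. The boundary applies to safety endpoints, in the plural, and the main Discussion makes thromboembolic complications one of them. Read together, these could put thromboembolism at the Z = 2 boundary already. The termination rule is also limited to events "possibly liable to the study product", which may leave out bleeding that has nothing to do with the product. The DSMB receives SAE line listings every three months and reviews interim and final safety data. Deaths and suspected unexpected serious reactions are reported to the sponsor in real time.

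Much of this stands, and it limits the point. A reader might infer that a bleeding benefit would hide a thromboembolic harm outright. The documents do not support that. Near-complete cancellation needs a high critical-bleeding rate that they do not give, and other routes to detection exist.

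A reader might also infer that a non-significant SAE total would be taken as proof of safety at the end. Nothing says so. Thromboembolic events, troponin, ECG and hepatic vessel ultrasound are recorded as safety parameters, and categorical data are to be compared between groups.

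What the reply does not repair is the wording of the criteria. Both places that say when to stop for harm name only (serious) adverse events. The attribution qualifier appears in one of them and rests on judging causality. No sentence states that thromboembolic events are compared separately at the boundary.

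**Conclusion.** The point holds as a badly fixed criterion. Read as written, a comparison of undifferentiated SAEs is much less sensitive to the harm the protocol singles out: about 2% to 28% against 47% at the interim, for an assumed rise in thromboembolism from 5% to 20%. Background SAEs at 30% are enough to bring it to 13% without any bleeding effect.

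The size rests on assumed rates, independent components and a literal reading of the two criteria. Under the reading in which thromboembolism is already a separate endpoint at the boundary, the loss disappears and only the wording needs correcting. The masking is therefore possible and partial, not certain.

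**What to change.** In Interim analysis and in Premature termination of the trial, state that the harm boundary is applied to thromboembolic events as a separate comparison, at both the interim and the final analysis. Define these as arterial and venous events, including hepatic vessel thrombosis. Report the risk difference with its 95% confidence interval each time.

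Keep the comparison of total SAEs, and show it with and without critical bleeding. Bleeding should not be dropped from the harm data: the Background lists disseminated intravascular coagulation among the possible complications of PCC, so an excess of bleeding must stay visible as harm.

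The events and the supporting examinations are already recorded, so the change costs wording in the protocol and the DSMB report. The downside is one more harm comparison. Under no true difference, Z = 2 in the harm direction has a nominal chance of about 0.0455 / 2 = 2.3% per comparison and look, so false alarms rise somewhat.
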